## Abstract

**Background:**

Total Knee Arthroplasty (TKA) remains the gold standard for treatment of debilitating symptoms of knee osteoarthritis (OA). Even though providing satisfactory results for the majority of patients, some studies report dissatisfaction after TKA to be as high as 20%. Among other things, pain catastrophising and self-efficacy are thought to compromise results of TKA. Implant manufacturers keep improving upon their designs in an attempt to improve functional outcomes. One of these novel knee systems is the Attune. To our knowledge, there are no clinical follow-up studies reporting results of the uncemented version. The main objective of this multicentre prospective observational study is to evaluate revision rate, complications, radiographic outcomes (i.e. alignment and radiolucent lines) and patient reported outcomes of the uncemented Attune mobile bearing TKA. Secondary objectives are (1) to assess physical function, return to sport and return to work after TKA and (2) to evaluate the long-term effect of preoperative psychological factors on satisfaction after TKA.

**Methods:**

All patients presenting in the participating centres with knee pathology warranting joint replacement therapy will be considered for inclusion, an absolute indication for cemented fixation is the only exclusion criterium. Evaluation of clinical and radiographic performance (e.g. radiolucent lines) is done at 6 weeks, 6 months, 1 year, 5 years and 10 years after surgery using validated patient reported outcome measures. Cumulative revision rates are calculated after 5 and 10 years using Kaplan–Meier methods. Physical function is assessed with performance based measurements before and 1 year after surgery. Return to sports is assessed using the Tegner and University of California Los Angeles (UCLA) activity rating scale before and 1 year after surgery. Return to work is evaluated by inviting patients of working age to complete a short questionnaire 1 year after surgery. Psychologic factors are assessed using questionnaires for pain catastrophising, pain self-efficacy and mental health before, 5 years and 10 years after surgery. Preoperative psychologic scores are correlated to functional outcomes.

**Discussion:**

The current study aims to report the clinical performance of a novel implant and can help provide insight in factors that play a role in satisfaction after TKA.

**Trial registration:**

ClinicalTrials.gov identifier: NCT04247672 (January 30, 2020)

## Background

Every year, 1.5 million total knee arthroplasties (TKA) are performed worldwide in patients whose joints have been severely affected by osteoarthritis, rheumatoid arthritis, or trauma, causing intense pain and loss of function. Due to the ageing society, these numbers are expected to increase with up to 43% by 2050 [1]. Even though joint replacement provides satisfactory and durable results for most patients, up to 20% are thought to still not be satisfied with their artificial joint [2]. Preoperative mental status and related pain coping have been identified as factors that may lead to dissatisfaction [3]. A review by Baert et al. identified catastrophic thinking and poor coping capabilities to predict more pain after TKA, whereas evidence on the impact on knee function remains conflicting in nature [3]. Most studies assess this influence only 1 year after surgery, with the study by Brander et al. prolonging the follow-up to 5 years [4]. Whether pain catastrophising remains a significant predictor of dissatisfaction at long-term follow-up remains to be elucidated.

Besides surgical performance, patient characteristics and expectation management [5], several knee systems have been developed in an attempt to improve functional outcomes. One of these models is the uncemented Attune knee system (DePuy, Warsaw, Indiana, USA), first implanted in October 2016. One of the landmark features is a gradually reducing radius in the geometry of the femoral component, more closely mimicking the anatomical patellofemoral joint and facilitating more natural femoral rollback during flexion [6–8]. Its predecessor (Low Contact Stress, DePuy, Warsaw, Indiana, USA) had excellent results [9], but it is still unclear whether the newer, more costly, Attune outperforms it. Comparisons of the cemented Attune with previous knee systems show promising results in terms of patellofemoral outcomes [10–13], but fail to demonstrate definitive superiority in terms of all patient reported outcomes [10, 11, 14–19]. An important note is that all cited studies compare posterior stabilized implants, which are significantly different with regards to patellofemoral kinematics compared to cruciate retaining designs [20]. Clinical superiority of the Attune tends to abate with longer follow-up, implicating a possible advantage in short-term recovery and return to activities. There is no follow-up study reporting the results of the uncemented Attune. Moreover, all previously cited studies report better patellofemoral outcomes with patellar resurfacing, making it still unclear whether the implicated superior design changes of the femoral component hold ground without patellar resurfacing. Due to the significant differences in costs, the proposed superiority needs more scientific scrutiny to justify the higher implant price.

The primary objective of the current multicentre prospective cohort study is to report survivorship, complications, radiographic outcomes (i.e. alignment and radiolucent lines) and patient reported outcome measures associated with the uncemented Attune mobile bearing (“rotating platform”) cruciate retaining knee system without patellar resurfacing. Secondary objectives are (1) assess return to activities (work and sports) after TKA and (2) analyse preoperative psychologic factors and their influence on patient satisfaction following TKA.

## Methods/Design

### Study design

The current study is a prospective cohort study. Patients will be recruited from high-volume TKA orthopaedic departments in the following 6 hospitals in the Netherlands:Spaarne Gasthuis, Hoofddorp (3 participating surgeons with extensive experience with uncemented fixation), coördinating siteBergman clinics, Rijswijk (2 participating surgeons with extensive experience with uncemented fixation)Medisch Spectrum Twente, Twente (2 participating surgeons with limited experience with uncemented fixation)Maastricht Universitair Medisch Centrum, Maastricht (2 participating surgeons with limited experience with uncemented fixation)Alrijne Ziekenhuis, Leiderdorp (2 participating surgeons with average experience with uncemented fixation [limited to unicondylar knee arthroplasty])Bravis Ziekenhuis, Bergen op Zoom (1 participating surgeon with extensive experience with uncemented fixation)

All surgeons with limited experience regarding uncemented TKA fixation are extensively trained by experienced colleagues and the implant manufacturer before participation in the study.

### Patient selection

The population will consist of patients with symptomatic knee pathology warranting joint replacement therapy (i.e. primary, secondary and traumatic osteoarthritic knees with or without previous arthroscopic or open knee surgery). To be eligible for inclusion, a subject must be between 21–90 years old and capable of understanding and complying with study procedures. A patient will be excluded if there is any absolute contra-indication for uncemented fixation at discretion of the surgeon (e.g. decreased bone stock/quality of the spongiosa), there is an indication for primary revision arthroplasty (e.g. stemmed components) or if the patient is unwilling to sign informed consent or comply with follow-up procedures. The patient is informed and recruited by the treating orthopaedic surgeon. After being informed verbally and in writing by the treating surgeon and the research nurse, the patient is given a mandatory reflection period of 14 days. Thereafter, the informed consent form is signed first by the patient and secondly by the surgeon or his/her designated staff (e.g. research nurse).

### Surgical procedure

All surgeons participating in the study are properly trained for the Attune knee system according to the instructions of the implant manufacturer (DePuy Synthes, Warsaw, Indiana, USA). To avoid bias, all participating surgeons will use the same surgical techniques. A tourniquet is never used and surgery is performed under spinal anaesthesia. A standard medial parapatellar incision with a medial arthrotomy is used. All knees are mechanically aligned with intramedullary (femur) and extramedullary (tibia) alignment guides. Gap balancing methods and ligament releases are used to balance the knee. An additional release of the posterolateral capsule is performed for fixed valgus knee deformities. Osteophytes are removed around the patella and it is radially circumcised with electrocauterization, a lateral release or facetectomy is performed when indicated by the surgeon. The patella is only resurfaced if strictly indicated by the surgeon thus it is not standard care. Local infiltration analgesia (LIA), active prevention of postoperative nausea and vomiting (PONV) and immediate postoperative mobilization under the supervision of a physical therapist are routinely offered to ensure fast rehabilitation. Thrombosis prophylaxis is according to the standard of care of the participating institution. Follow-up will be scheduled at 6 months, 1 year, 5 years and 10 years after surgery.

### Implant design

All patients are receiving the uncemented, mobile bearing (“rotating platform”), cruciate retaining configuration of the Attune primary knee system (DePuy Synthes, Warsaw, Indiana, USA) (Fig. 1). The femoral component has been reshaped (trochlear groove accommodates patient variation in patellar tracking and a gradually reducing radius to provide anteroposterior stability during full range of motion). The tibial tray contains four pegs that are positioned radially around a central cone which, in synergy with an optimized porous coating pattern, reduces micromotion of the tibial tray and thus optimizes initial uncemented fixation. The size range has been expanded to accommodate patient variation and the polyethylene is better designed to deliver durable oxidative stability.

**Fig. 1 Fig1:**
[figure not shown]
Oblique (**a**) and anteroposterior (**b**) view with landmark features of the uncemented Attune mobile bearing (“rotating platform”) implant (DePuy Synthes, Warsaw, Indiana, USA). A gradually reducing radius of the femoral component (1) allows for more stability during flexion. The patellofemoral surface of the femoral component mimic the original anatomy more closely (2), providing more natural kinematics and patellar tracking during knee flexion. A porous coating on the 4 pegs and proximal part of the central cone provides an ideal environment for fixation (3). Images provided courtesy of DePuy Synthes

### Main outcomes – revision rate, complication rate, alignment, radiolucencies and PROMs

The main outcomes are revision rate, complication rate and patient reported outcome measures (PROMs) at 1 year, 5 years and 10 years after index surgery (Table 1). Revision is defined as any alteration to the implanted knee (e.g. implantation, explantation or replacement) including at least one component. Revision is further divided into major revisions (exchange or explantation of metal components) and minor revisions (exchange of insert or placement of patellar prosthesis).

**Table 1 Tab1:** Study procedures and distribution of the different outcomes in the follow-up schedule

	Preoperative	6 months	1 year	5 years	10 years
Patient reported outcome measures	X	X	X	X	X
Return to sports and physical function					
Tegner / UCLA activity scale	X		X		
Performance based measurements	X		X		
Return to work			X		
Radiographic analysis					
Radiolucent lines		X	X	X	X
Alignment	X		X		
Psychologic factors	X		X	X	X

N.B. Patients are routinely seen at the 6 week follow-up mark in some of the participating centres, no study parameters are registered at this visit

Complications are represented by any adverse event related to the knee surgery arising in the postoperative period. Complications are either major (e.g. prosthetic joint infection, reoperation other than revision, bearing dislocation/spin-out, manipulation under anaesthesia, venous thrombo-embolism) or minor (e.g. superficial wound infection, delirium).

Alignment is assessed on long-leg full weight bearing bilateral conventional radiographs before surgery and at the 1 year follow-up mark according to the parameters proposed by Hadi et al. (Table 1) [21]. Alignment parameters that are assessed include: sagittal and coronal tibial angle (sTA and cTA); sagittal and coronal femoral angle (sFA and cFA); coronal tibio-femoral mechanical angle (cTFmA), coronal tibiofemoral anatomical angle (cTFaA). All radiographs are furthermore assessed for progressive radiolucent lines at all time points according to the Knee Society Total Knee Arthroplasty Roentgenographic Evaluation and Scoring System [22].

Patients are asked to complete questionnaires before surgery and at every follow-up visit, which consists of 6 validated PROMs (Table 1). The EuroQol 5D-5L is a validated questionnaire for general health [23]. The Oxford Knee Score (OKS) is a validated and extensively used 12-item questionnaire for the subjective evaluation of knee function and pain [24, 25]. The Forgotten Joint Score 12 (FJS-12) is a knee specific questionnaire to assess joint awareness during daily living and has less of a ceiling effect when compared to other knee specific PROMs (e.g. patients ‘forget’ about a well-functioning joint) [26, 27]. Patellofemoral pain and function will be assessed with the Kujala Anterior Knee Pain Scale (AKPS) [28–30]. Finally, patients are asked to rate their pain (during activity and rest) and satisfaction concerning the TKA on a Numeric Rating Scale (NRS). All questionnaires are supplemented with 2 anchor questions that measure change in pain and daily function since index surgery.

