### Statistical analysis

Sample size calculation was aimed at non-inferiority of the Attune knee compared to the LCS knee, the predecessor of the Attune. A non-inferiority margin of 1.5% was assumed. Survival data of the LCS was extracted from a meta-analysis on long-term survivorship studies of the LCS TKA (mobile bearing cemented and uncemented implants) [45]. Pooled 10 year survivorship of the LCS was 98.1% [45]. Based on α = 0.05, power (1-β) of 0.90 and both true proportion (p) and null hypothesis proportion (p0) of 98,1%, a sample size of *n* = 709 was calculated with a one-sided test [46, 47]. Taking drop- outs and death within 10 years into account (approximately 20–25%), we are aiming for inclusion of *n* = 900 knees.

All data will be collected in Research Manager (Cloud9 software, Deventer, Netherlands) and exported for analysis to SPSS Statistics 26.0 (IBM SPSS, New York, USA). Data is coded and the encryption key is stored on the local hospital server of the participating institution. Statistical analysis will be mainly descriptive. Baseline characteristics and results will be described as means with standard deviations (SD) or 95% confidence intervals (95% CI), medians with interquartile ranges (IQR) or frequencies with accompanying proportions. Revision rates will be calculated by use of Kaplan–Meier survival analysis and competing risk analysis, where death is considered a competing risk [48]. Multivariable Cox proportional hazard analyses will be performed to assess the influence of radiolucent lines and implant alignment on implant survival and hazard ratios (HR) with 95% CI will be calculated. Mixed model analysis for repeated measures will be used for assessment of change in PROMs scores during follow-up. Multivariate linear regression analysis will be used to assess the association of radiolucent lines, implant alignment and preoperative psychologic scores (PSEQ, PCS and PHQ-2) with PROMs after 1, 5 and 10 years after index surgery.

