### Data monitoring

The coordinating site (Spaarne Gasthuis) is responsible for data monitoring. Due to a very low additional risk the study brings, the medical ethics committee concluded that no data monitoring committee is necessary. All (serious) adverse events related to the implant are reported by the coordinating site to the medical ethical committee within 7 (serious adverse events) or 15 (adverse events) days.

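### The complication outcome is limited to postoperative events, so a surgery-related event that occurs and is resolved during the index operation is not counted directly in any main outcome

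*Protocol article*

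**What the plan says.** The Background section makes complications of this implant part of the primary objective. The section on main outcomes then states: "The main outcomes are revision rate, complication rate and patient reported outcome measures (PROMs) at 1 year, 5 years and 10 years after index surgery". It defines the complication outcome in one sentence: "Complications are represented by any adverse event related to the knee surgery arising in the postoperative period". The examples given for major complications are "prosthetic joint infection, reoperation other than revision, bearing dislocation/spin-out, manipulation under anaesthesia, venous thrombo-embolism"; those for minor ones are superficial wound infection and delirium. The lists are illustrative, but none of the examples is specific to the operation itself.

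Revision is defined separately: "Revision is defined as any alteration to the implanted knee (e.g. implantation, explantation or replacement) including at least one component".

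Outside the outcomes, the Data monitoring section states: "All (serious) adverse events related to the implant are reported by the coordinating site to the medical ethical committee". That sentence sets no limit to the postoperative period.

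The article defines no intraoperative outcome and gives no intraoperative event rate.

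**The concern.** The study is meant to describe how a new uncemented design performs, and the Background section says that no follow-up study of it exists. An intraoperative fracture, or a component that cannot be fixed without cement and is changed before the operation ends, bears directly on that aim. (These events are my examples; the article does not name them.) Under the definition as written, such an event arises too early to be a complication.

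The Study design section adds some weight. Of the 12 participating surgeons, 4 have limited experience with uncemented fixation and 2 have average experience confined to unicondylar knees, so half are not described as having extensive experience. The article says that surgeons with limited experience are trained before they take part, but events at the operation remain of interest.

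At stake is the meaning of the published complication rate. A reader may take it to cover everything that went wrong because of the surgery, when it starts only after the operation.

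**Working it through.** The main question is one of definitions, so I follow one hypothetical knee through them. An event caused by the surgery occurs during the index operation, is dealt with before the operation ends, and has no later consequence.

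1. **Complication.** The event is related to the surgery but did not arise postoperatively. Not counted.
2. **Revision.** The definition concerns alteration to a knee that has been implanted. A change made before the index operation is complete is not clearly a revision. Not clearly counted.
3. **Radiolucent lines, alignment and PROMs.** These may show consequences of an event. They do not count the event, and here there is no consequence to show.
4. **Table 1.** It has no operative column. It also has no row for complications or revisions, so this is weak evidence either way.
5. **Reporting to the ethics committee.** It has no postoperative limit and may pick up the event, but only if the event is related to the implant. It is safety reporting, not a study outcome.

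Such an event is therefore not counted directly in any main outcome.

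**Possible size.** The only input from the article is the target of 900 knees. The intraoperative rate r is my assumption. Uncounted events = 900 × r:

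| Assumed r | Events in 900 knees |
|---|---|
| 0.1% | 900 × 0.001 = 0.9 |
| 0.5% | 900 × 0.005 = 4.5 |
| 1% | 900 × 0.01 = 9 |
| 2% | 900 × 0.02 = 18 |

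To show the effect on a reported rate, suppose also that the postoperative complication rate is b = 5% and that the two kinds of event are independent. The combined rate is b + r − b × r:

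- r = 0.1%: 0.05 + 0.001 − 0.00005 = 5.1%
- r = 0.5%: 0.05 + 0.005 − 0.00025 = 5.5%
- r = 1%: 0.05 + 0.01 − 0.0005 = 5.95%
- r = 2%: 0.05 + 0.02 − 0.001 = 6.9%

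Both b and r are assumptions, so these figures give scale only.

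**Does anything in the sample size change?** The Statistical analysis section uses a 10-year survivorship of 98.1%, a margin of 1.5 percentage points, one-sided α = 0.05 and power 0.90. With the usual one-sample formula:

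n = p(1 − p) × ((z₀.₉₅ + z₀.₉₀)/margin)² = 0.981 × 0.019 × ((1.645 + 1.282)/0.015)² ≈ 709.4

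This agrees with the stated 709. For loss, 709/0.80 gives 887 and 709/0.75 gives 946; the target of 900 corresponds to a loss of 1 − 709/900 = 21.2%. All these inputs concern implant survival and none concerns complications, so changing the complication definition leaves these figures as they are.

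**The case against.** The strongest reply is that the definition is explicit and openly stated. For the outcome it defines, the rate is not biased; it is simply a postoperative rate. The analysis is described as mainly descriptive, and no margin, comparator or test is attached to complications. An intraoperative problem that later leads to reoperation counts as a major complication, and one that leads to component exchange counts as a revision. The article also names aseptic loosening as the main criticism of uncemented fixation, and it addresses that through revision and radiolucent lines. All of this stands. What remains uncovered is the event that is resolved at the operation and leaves no counted trace.

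A second reply is that an article condenses a fuller protocol. That would answer a complaint about missing detail on operation forms. It does not answer this point, because the sentence given in the article itself fixes the time limit.

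A reader might infer three stronger points that the article does not support.

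- **Converted knees leave the cohort.** The implant section says "All patients are receiving the uncemented, mobile bearing (“rotating platform”), cruciate retaining configuration of the Attune primary knee system", and the exclusion criteria include "any absolute contra-indication for uncemented fixation at discretion of the surgeon (e.g. decreased bone stock/quality of the spongiosa". The first describes the device and does not define an analysis set. The second is listed with the eligibility criteria, and nothing says that it is applied during surgery or removes a consented knee. The article therefore does not show that the revision cohort is selected for good bone.
- **The non-inferiority question is threatened.** "A non-inferiority margin of 1.5% was assumed" refers to survivorship. Missed complications cannot be set against it.
- **The complication rate is shown to be too low.** It is lower than a perioperative rate only if uncaptured events occur, and the article gives no frequency for them.

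**Conclusion.** The point holds in a limited form. The stated rule excludes surgery-related events that arise during the index operation, and no other main outcome counts them directly, although complications of this implant belong to the primary objective. If such events occur without a later counted event, the published rate will understate perioperative complications. The amount cannot be derived from the article: about 1 to 18 events in 900 knees rests wholly on an assumed rate of 0.1% to 2%. No stated figure is wrong. This is a definition worth correcting because the correction is cheap, not an error that undermines the study.

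**What to change.** Define a complication as any surgery-related adverse event that arises during or after the index operation, and record intraoperative events on the operation form. Use as the denominator for the complication rate all consented knees taken to surgery with intent to implant the uncemented Attune. Report as a separate count those knees that were converted during surgery to another fixation or implant. This concerns counting and reporting only.

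If the sponsor prefers to keep the present definition, the outcome should at minimum be labelled as postoperative complications wherever it is reported.

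The cost is one or two items on the operation form and a complication rate that may look slightly less favourable. The sample size and the survival analysis need no change.
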